### Sample size {14}

According to clinical experience, the effective rate of NERD in the TCM group was P1 = 92.0%. The NERD effective rate of the western medicine group was P2 = 61.2% [(two-sided type I error rate of 0.05, *α* = 0.05); (one-sided type I error rate of 0.20, *β* = 0.20)]. The sample size is calculated by the following formula:
$$ n=\frac{2\overline{p}\overline{q}{\left({Z}_{\alpha }+{Z}_{\beta}\right)}^2}{{\left(P1-P2\right)}^2} $$

*n*1 = *n*2 = 2 × 0.766 × 0.234 × 2.8^2^ ÷ 0.308^2^ = 30. Taking approximate dropouts of 20% into account, the number of participants recruited was estimated to be 36 per group. Therefore, a total of 72 patients will be recruited in this trial. And we will additionally recruit 10 healthy controls.

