### Statistical analysis {20}

Efficacy analysis will be performed based on both FAS and PPS patients. Safety analysis includes all randomized participants who take at least one bag of HWJNR and have data for safety assessment. Comparing the healthy control group with the traditional Chinese medicine group, we will study the composition of the intestinal flora and the expression of metabolites in patients with NERD and the healthy group. And it will also reveal the mechanism of action and advantages of HWJNR in the treatment of NERD patients.

Changes from baseline to post-treatment in GERD-Q, SF-36, PRO, and syndrome score of TCM will be analyzed using analysis of covariance with associated 95% confidence intervals. All the analysis results will be generated by SPSS 25.0 software. Repeated measurement data are expressed by mean ± standard deviation, intra-group comparison is performed by analysis of variance of repeated measurement data, and inter-group comparison is by multivariate analysis of variance (MANOVA). *P* ≤ 0.05 indicates that the difference is statistically significant. Unilateral test will be used in all statistical tests, and the significance level *P* ≤ 0.05. The arithmetic mean, standard deviation, median, minimum, and maximum will be calculated according to the data distribution. Counting data will be used to calculate the number and percentage of cases.

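### The plan tests everything one-sided at 0.05 although the trial was sized for a two-sided 5% error, which doubles the false-positive rate in favour of HWJNR

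*Protocol article*

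**What the plan says.** Two sections of the protocol article set the error rate.

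- **Sample size {14}** states a "two-sided type I error rate of 0.05" and β = 0.20, which it labels a "one-sided type I error rate of 0.20". The calculation is printed as "2 × 0.766 × 0.234 × 2.8^2^ ÷ 0.308^2^ = 30" per group.
- **Statistical analysis {20}** sets significance at P ≤ 0.05 and then adds: "Unilateral test will be used in all statistical tests, and the significance level" is again P ≤ 0.05.

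The Statistical analysis section also says that changes in GERD-Q, SF-36, PRO and TCM syndrome score "will be analyzed using analysis of covariance with associated 95% confidence intervals". It assigns within-group comparisons of repeated measurements to repeated-measures analysis of variance and between-group comparisons to MANOVA.

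The article gives no reason for one-sided testing, no direction for it, and no reduced one-sided level.

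**The concern.** The sidedness of the test decides what counts as a positive trial, and the article gives two incompatible answers.

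The analysis rule is the more lenient one. With a fixed level of 0.05, going from two-sided to one-sided puts the whole 5% in one tail. If that tail is superiority of HWJNR, the evidence required for a positive claim is weaker than the design assumed.

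The comparator makes this more serious. HWJNR replaces omeprazole, and the Background section describes proton pump inhibitors as first-line treatment for reflux disease. HWJNR doing worse than omeprazole is a real possibility, and a one-sided superiority test can never declare it. The Discussion expects the results to feed into guidelines.

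The rule also fails within its own section. It can disagree with the planned confidence intervals, and it cannot be applied to the F tests listed there.

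**Working it through.** **Inputs, all from Sample size {14}**

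- "the effective rate of NERD in the TCM group was P1 = 92.0"%, so P1 = 0.920.
- "The NERD effective rate of the western medicine group was P2 = 61.2"%, so P2 = 0.612.
- P1 − P2 = 0.308; mean rate p̄ = (0.920 + 0.612)/2 = 0.766; q̄ = 0.234.
- α = 0.05 two-sided; β = 0.20, so z_β = 0.842.

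**Step 1: reproduce the plan's figure.** The article's formula is n = 2·p̄·q̄·(z_α + z_β)² / (P1 − P2)².

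- With the printed 2.8: 2 × 0.766 × 0.234 × 2.8² / 0.308² = 29.6, rounded up to 30. This matches.
- With unrounded two-sided values (1.960 + 0.842): 29.7, rounded up to 30.

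The figure of 30 is therefore a two-sided 5% calculation in its arithmetic as well as in its label.

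**Step 2: put the analysis rule into the same formula.** One-sided 5% gives 1.645 + 0.842 = 2.49 in place of 2.80. Then n = 23.4, rounded up to 24. The rule in Statistical analysis {20} does not reproduce the stated 30.

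**Step 3: compare the decision rules for a directional contrast.**

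| | Two-sided 0.05 | One-sided 0.05 |
|---|---|---|
| Critical z | 1.960 | 1.645 |
| False-positive probability in favour of HWJNR | 0.025 | 0.050 |
| n per group for 80% power (article's formula) | 30 | 24 |
| Power at 30 per group | 82.1% | 89.6% |

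The ratio of false-positive rates is 0.050/0.025 = 2. Power is Φ[(0.308·√n − z_α·√(2p̄q̄)) / √(P1(1−P1) + P2(1−P2))]. At n = 30 the two-sided case is (1.687 − 1.960 × 0.5987)/0.5577 = 0.92, giving 82.1%. The one-sided case is (1.687 − 1.645 × 0.5987)/0.5577 = 1.26, giving 89.6%.

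**Step 4: check against the planned confidence intervals.** A conventional 95% interval excludes zero only when the estimate exceeds 1.960 standard errors. An estimate between 1.645 and 1.960 standard errors in favour of HWJNR has a one-sided P between 0.025 and 0.05. It would be declared significant while its interval includes no difference. For example, a one-sided P of 0.04 corresponds to a two-sided P of 0.08.

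**Step 5: check against the named tests.** The outcomes are recorded at baseline, week 4 and week 8. A repeated-measures F test over three time points, or a MANOVA across several measurements, has no direction. A one-sided version of these is undefined, so a rule covering all tests cannot be carried out.

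**The case against.** The contradiction itself is hard to dispute. The objections concern what follows from it.

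- **The doubling is conditional.** It applies to directional contrasts such as the ANCOVA group effect, and only if they are run in favour of HWJNR. The F tests keep their usual 5% error. The article prints no direction; favouring HWJNR is inferred from P1 > P2. This stands as a qualification, but an unstated direction is no comfort, since it could be chosen after the data are seen.
- **Inferiority would still be visible.** A conventional 95% interval would show HWJNR to be worse. That is correct. What is lost is the ability of the formal test to declare it.
- **The interval conflict assumes two-sided intervals.** The article does not say so. It is the natural reading, but it is an assumption.
- **Safety and omics tests.** The word covering all tests reaches them formally, but the article names no test for either, so no identified analysis is affected.
- **The 24 against 30 comparison concerns an effective rate.** The primary outcome is the week-8 GERD-Q score, for which no difference or standard deviation is given. The comparison shows the inconsistency of sidedness; it does not give the power for GERD-Q.
- **It may be a translation slip.** The article has others, such as calling β a type I error. That is plausible, but the printed decision rule would still be wrong and need the same correction.

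A separate analysis plan would not settle the matter, because the point is a stated rule that contradicts the stated design.

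**Conclusion.** The concern holds. Sample size {14} uses a two-sided 5% error, confirmed by its own arithmetic, and Statistical analysis {20} prescribes one-sided tests at 5%. Both cannot apply.

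For each directional comparison, the probability of a false claim for HWJNR is 5% where the design implies 2.5%. The critical value is 1.645 where the design implies 1.960. This rests on two readings: the one-sided tests are directed at superiority of HWJNR, and the 95% intervals are conventional two-sided ones. The contradiction between the two sections, and the impossibility of one-sided F tests, depend on neither.

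This must be corrected because it sets the threshold for a positive result.

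**What to change.** In Statistical analysis {20}, replace the sentence on unilateral testing with: *All tests are two-sided at the 0.05 level; the primary comparison is reported with a two-sided 95% confidence interval.* One-sided testing at 0.025 with the direction stated would also agree with the sample size for directional contrasts. It would still leave the F tests without a usable rule, so the two-sided wording is cleaner.

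The cost is one sentence and a slightly stricter threshold. The printed calculation needs no extra patients for this change, since 30 evaluable per group was already computed two-sided. Whether that number suffices for the GERD-Q score cannot be judged from the article.

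Recruitment had already begun when the article was submitted, so the correction should be made and dated before the database is locked and before anyone sees results by group.

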### Data monitoring {5d, 21, 23}

Independent clinicians and biostatisticians with extensive research experience in clinical trials will serve as the Data and Safety Monitoring Committee. Two independent data administrators perform dual data entry and proofreading. The primary researchers, data administrators, and biostatisticians will check, confirm, and lock the database before data processing. Only data administrators and biostatisticians will have access to the final data. The Ethics Committee of Dongfang Hospital will conduct annual audits and supervise protocol, adverse effects reporting, and interim results. Researchers will submit research progress reports within 1 month before the deadline.

### Adverse event reporting and harms {22,30}

An adverse event (AE) refers to any adverse medical event that occurs to the patient or clinical investigation object during the period of management of drugs, but it does not necessarily have a causal relationship with this treatment. According to the standards developed by the Adverse Drug reaction Supervision Center of the Ministry of Health, we will classify them according to the five-level classification of “affirmative, probable, probable, suspicious and impossible.” The former four will be taken together to study the AEs of drugs, and the incidence of AEs will be calculated accordingly (Table 5).

**Table 5 Tab5:** Adverse drug reaction supervision center of the Ministry of Health. Evaluation criteria for the relationship between AE and research drug use

Judgment index	Judgment result				
	Definitely	Probably	Probably	Suspiciously	Impossible
1. Whether there is a reasonable relationship between the time of starting medication and the time of suspicious occurrence.	+	+	+	+	+
2. Whether the suspected ADR (ADR) conforms to the known ADR type of the drug	+	+	+	−	−
3. Whether the suspected ADR can be explained by the patient's pathological condition, combined medication, therapy or previous therapy.	−	−	±	±	+
4. It is doubtful whether the withdrawal or reduced dose of ADR alleviates or disappears	+	+	±	±	−
5. Does the same reaction occur again after re-exposure to suspicious drugs	+	?	?	?	-

Description: + for positive, − for negative, ± for positive or negative, ? indicates that the situation is unknown

Before the trial, no AE has been reported in the clinical application of HWJNR. The possible AEs of omeprazole enteric-coated tablets include diarrhea, headache, nausea, abdominal pain, flatulence and constipation, and occasional increase of serum aminotransferase (ALT, AST), rash, dizziness, and so on. These AEs are usually mild and can disappear automatically, which have nothing to do with the dose. Since the omeprazole enteric-coated tablets used in this study belong to the routine treatment of NERD, these AEs may also occur even if the subjects do not participate in the clinical study. During the study, we will closely monitor AEs and take measures to prevent them. Once the emergencies related to the study occur, the research assistant will record the detailed information including symptoms, signs, severity, start date, duration, lab results, intervention, and the results of adverse events at each visit. And the subjects will have the right to receive corresponding compensation.

Serious adverse event (SAE) refers to any adverse medical accident that occurs at any dose, including death, life-threatening conditions, the need for hospitalization or prolongation of existing hospitalization, persistent or significant disability/incapacity, or congenital anomaly/birth defect. Once SAEs occur, the events must be reported to the principal investigator and the Ethics Committee and the Beijing Food and Drug Administration within 24 h. The principal investigator has the power to terminate the trial if necessary.

## Discussion

The study is a single-center, randomized controlled, double-blind, placebo-controlled clinical trial for HWJNR to evaluate the efficacy and safety in the treatment of NERD. NERD is characterized by the presence of typical GERD symptoms associated with pathological acid reflux, including heartburn and regurgitation, but the absence of esophageal erosion [21, 22]. NERD presents in approximately 70% of patients with GERD, which has a great impact on life quality [3]. The high incidence of NERD and the widespread use of PPIs in clinical practice mean that the problems of complications and recurrence after drug withdrawal are increasingly common. TCM has a significant role in alleviating symptoms and maximizing quality of life of NERD patients. Hence, GERD-Q, SF-36, PRO, and syndrome score of TCM will be selected as therapeutic indicators, since they are correlated to the patients’ symptoms and quality of life.

HWJNR is mainly made up of Huangqin, Huanglian, Qingbanxia, Ganjiang, and other ten herbs. In our previous research, HPLC analysis was used to measure the contents of HWJNR. The results showed that the repeatability and stability of these main ingredients of HWJNR are good, and the quality is controllable [18]. Previous clinical studies have shown that HWJNR is safe and effective in NERD.

The factors that affect NERD have not yet been clarified [23]. There are several hypotheses about the etiology of NERD, such as esophageal visceral hypersensitivity, sustained esophageal contractions, and abnormal tissue resistance [24]. Recently, studies focus on abnormal microbial-brain-gut interaction and low-level inflammation of GERD mediated by hypoxia-inducible factor [25, 26]. We also expect to have a deeper understanding of the dominant links of treatment, reveal the potential mechanism of HWJNR, and study the composition structure and metabolite expression profile of intestinal flora in patients with NERD.

We aim to provide new and high-quality evidence in HWJNR for patients with NERD (cold-heat complex syndrome) through the clinical trial. The research results are expected to help formulate relevant clinical programs and corresponding guidelines. However, this study is a small sample size clinical study conducted in Beijing of China. Therefore, it is necessary to conduct multicenter clinical trials in further research.

## Trial status

This updated version of the trial protocol (version 2.0, 11 November 2020) has been reviewed and approved by the Ethics Review Committee of Dongfang on 7 December 2020. All relevant researchers have completed the standardization training concerning this trial in December 2020. The first patient was recruited in the trial on 15 January 2021. By the time our manuscript was submitted, we had recruited 10 volunteers. Recruitment is scheduled to be completed in December 2022.

## Abbreviations

AE: Adverse event
BE: Barrett esophagus
CRF: Case Report Form
FAS: Full Analysis Set
GERD: Gastroesophageal reflux disease
GERD-Q: Gastroesophageal reflux disease health-related quality of life questionnaire
HWJNR: Hewei Jiangni recipe
ICF: Informed Consent Form
ITT: Intention-to-treat
NERD: Nonerosive gastroesophageal reflux
MANOVA: Multivariate analysis of variance
PPI: Proton pump inhibitor
PPS: Per-protocol set
PRO: Patient-reported outcomes
P-CAB: Potassium-competitive acid blocker
RCT: Randomized controlled trial
RDQ: Reflux Diagnostic Questionnaire
RH: Reflux hypersensitivity
SPIRIT: Standard Protocol Items: Recommendations for Interventional Trials
SAE: Serious adverse event
SAP: Symptom association probability
SF-36: SF-36 quality of life scale
SS: Safety set
TCM: Traditional Chinese medicine
TIF: Transoral incisionless fundoplication
TLESR: Transient lower esophageal sphincter relaxation
